### Intervention and standard of care

The oral health care programme is a practice-led intervention that was developed by a multidisciplinary team of healthcare professionals and researchers (physicians, nurses, dentists, dental hygienists, and a dietitian), and in close collaboration with HNC survivors. The intervention starts 6 months after completion of RT and ends after the 3-year follow-up. Every 3 months, participants in the intervention group are scheduled for an appointment with a dental hygienist. During these visits, participants are asked about oral hygiene habits, fluoride use, dietary habits (with focus on intake of easily degradable carbohydrates), and oral dryness. The dental hygienist also performs a thorough examination of the oral cavity, assessing signs of dental problems (e.g., tooth decay) or gum problems (e.g., gingivitis or periodontitis).

The intervention is individually tailored and based on the examination and the patient’s report. It includes oral and written advice, and recommendations from the dental hygienist, e.g., how to increase oral hygiene using the correct toothbrushing technique, interdental cleaning, or strategies to address oral dryness. It also includes tailored preventive professional oral hygiene treatment, e.g., plaque and dental calculus removal, fluoride gel application, and polishing to produce a smooth and clean surface. All visits to the dental hygienist are at no cost. If oral problems are beyond the competence of the dental hygienist, dentists are consulted and the participant pays for any necessary treatment.

At the 6-month follow-up, patients are randomised to receive the intervention (oral health care programme) or standard of care, which in Sweden only includes dental care for up to approximately 3 months following treatment. Within standard of care, patients therefore need to actively seek dental care and support themselves after 6 months. Patients who have undergone RT targeting the oral cavity may be entitled to a partial allowance, which subsidies preventive dental care; however, not all patients receive this benefit, and it does not cover all the costs.

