#### Data collection overview

Clinical/research nurses, dentists and dental hygienists at each site are responsible for the data collection. Data are collected from all participants at baseline, 6 months after the end of treatment (randomisation and start of intervention), and 1, 2 and 3 years after randomisation. Non-adherence and non-retention are registered.

Data gathered through history taking or medical records include, e.g., demographics (sex, age and education), as well as information on diagnosis and treatment (tumour site and stage, treatment modality, comorbidities and medication), work ability and sick leave, eating ability, and habits, including use of nicotine and alcohol, nutritional status (anthropometrics, body composition). Body composition measurements using calf circumference are performed on all participants. Bioelectrical impedance analysis (Bodystat^®^ Multiscan 5000) is used on a subgroup.

In addition, participants complete questionnaires (PROMs) to assess HRQoL, depression, anxiety and stress, health status, self-efficacy, and self-rated oral health (Table 1). The questionnaires are completed digitally or on paper.

**Table 1 Tab1:** Data overview from patient-reported outcome measures, PROMs

Questionnaire	Description
European Organization for Research and Treatment of Cancer Quality of Life Questionnaire-Core 30 (EORTC-C30) [26]	Assesses health-related quality of life in cancer patients. Comprises 30 items covering, e.g., global health status, functional domains (physical, role, emotional, cognitive, and social), symptom scales (fatigue, pain, nausea/vomiting).
EORTC-Head and Neck Cancer Module (EORTC-HN43) [27]	Assesses health-related quality of life in patients with head and neck cancer, an updated version of HN35. Includes 43 items addressing disease- and treatment-specific issues, such as swallowing, speech, senses (taste and smell), pain, social eating, sexuality, and body image, as well as symptoms such as dry mouth and sticky saliva.
Depression Anxiety Stress Scale-21 (DASS-21) [28]	Measures negative emotional states. Consists of 21 items divided into three subscales assessing symptoms of depression, anxiety, and stress.
EQ-5D-3 L [29, 30]	Measures general health status. Consists of five dimensions (mobility, self-care, usual activities, pain/discomfort, and anxiety/depression). Each dimension has three levels of severity.

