General Self-Efficacy (GSE) [31]	Assesses an individual’s perceived ability to cope with a variety of demanding situations. Consists of 10 items measuring self-belief related to problem-solving and adaptation.
Self-Perceived Oral Health (SPOH) [32]	A modified version of the SPOH instrument is used to assess subjective oral health. The instrument includes items on self-rated oral health (12 items), oral health behaviours (8 items), perceived oral health knowledge (4 items), and future perspectives (2 items).

Data on oral health (number of remaining teeth, maximum interincisal opening [MIO], caries and periodontal status) are collected during clinical examination. Participants are asked how often they have sought dental care. Computed Tomography (CT) and Cone-Beam Computed Tomography (CBCT) are used to detect pathological changes in the jaw (osteoradionecrosis). Blood and saliva samples are collected for analysis and long-term storage (biobanking). Blood samples are analysed for haematology and immune parameters, including markers of inflammation. The stimulated whole salivary secretion rate is determined, and the buffering capacity is assessed. For a subgroup of participants, saliva composition (proteins, ions, metabolites and inflammatory biomarkers) and the oral microbiome will be analysed.

Register data will be obtained from the National Board of Health and Welfare (National Prescribed Drug Register, National Register of Care and Social Services for the Elderly and Persons with Impairments, National Register of Interventions in Municipal Health Care, National Cause of Death Register, National Patient Register, National Dental Health Register) and from the Swedish Social Insurance Agency (Micro Data for Analysis of Social Insurance [MiDAS] database, Dental care). Register data on healthcare utilisation will also be obtained for a subgroup of patients. Register linkage will be performed using personal identity numbers, and the data will be pseudonymised after data collection.

The collected register data will cover the period from one year prior to diagnosis to five years after the completion of treatment, and will include information about, for example, prescribed drugs, municipal health and social care, specialised outpatient and inpatient care, registered sickness absence, and costs related to functional impairments, as well as dental healthcare.

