### Data processing and analysis

The effects of the intervention will be evaluated in comparison with standard of care. Outcomes will be analysed using either change‑from‑baseline or end‑point values, depending on the nature of each variable. Time‑to‑event outcomes, where applicable, will use time from randomisation to the occurrence of the event of interest.

The main statistical analyses will be performed by statisticians according to the intention-to-treat (ITT) principle. The primary analysis of the EORTC QLQ-HN43 [27] will be conducted using an ANCOVA model adjusting for baseline values, with robust standard errors. Analyses will be performed at each follow-up time point, with the primary comparison at 12 months. To account for within-subject correlation, a linear mixed-effects model with random subject intercepts and a treatment-by-time interaction, using all three follow-up time points, will be used as a sensitivity analysis.

Missing data will be addressed using multiple imputation under the assumption that data are missing at random. Effect size will be estimated using Cohen’s d. Sensitivity analyses to assess the impact of non-compliance will include complete-case and per-protocol analyses. Descriptive statistics will be presented as numbers and percentages for categorical variables, and as means with standard deviation (SD) for continuous variables.

Resource use and societal costs will be used to investigate cost-effectiveness. The economic evaluation will be based on the direct medical costs of specialised healthcare (calculated from diagnosis-related group weights) and drug costs (the register includes costs for dispensed prescription drugs) among HNC survivors, as well as the direct non-medical costs of formal assistance services (assistance and home care, costed using templates from national and municipal statistics), costs for dental care, and indirect costs in the form of productivity loss for sickness absence, estimated according to the human capital approach. A subgroup analysis will be conducted using administrative data on primary care use from one healthcare region and unit costs for such use from national statistics, to identify the effect of including primary care in the evaluation. The economic evaluation will estimate societal costs over a one-year time horizon for each patient; no discounting will therefore be necessary in these analyses. Societal costs will be reported, as well as costs by components and payers.

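### Of the two analyses named for non-compliance, complete-case does not address it and per-protocol breaks the randomised comparison; a complier-average estimate should be added

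*Protocol article*

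**What the plan says.** All references are to the protocol article.

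- **Data processing and analysis** sets the principle: "The main statistical analyses will be performed by statisticians according to the intention-to-treat (ITT) principle". The primary model is a baseline-adjusted ANCOVA with robust standard errors, with the primary comparison at 12 months. On missing outcomes: "Missing data will be addressed using multiple imputation under the assumption that data are missing at random". It then gives one purpose to two further analyses: "Sensitivity analyses to assess the impact of non-compliance will include complete-case and per-protocol analyses".
- **Intervention and standard of care** describes what there is to comply with. In the programme arm: "Every 3 months, participants in the intervention group are scheduled for an appointment with a dental hygienist". For controls: "Within standard of care, patients therefore need to actively seek dental care and support themselves after 6 months".
- **Data collection overview** says what is recorded: "Non-adherence and non-retention are registered", and "Participants are asked how often they have sought dental care".

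The article defines no per-protocol population and gives no attendance threshold.

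**The concern.** The sentence states a question (what does non-compliance do to the result?) and names two analyses to answer it. Neither answers it well.

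Complete-case keeps a patient who missed every hygienist visit but returned the questionnaire. It drops a patient who attended every visit but did not return it. What it probes is the multiple-imputation step under missing at random.

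A per-protocol set does condition on compliance, but in this design the schedule of visits belongs to one arm only. Excluding patients for poor attendance therefore acts wholly or mainly on the programme arm, and what remains is no longer a randomised comparison. If attendance is related to how a patient would have scored anyway, the estimate mixes the programme's effect with that selection.

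At stake is the one result that would be read as the effect of the programme when it is followed. The primary result does not depend on it.

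**Working it through.** The plan gives no figure on this point, so there is none to reproduce. The check has four steps.

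**Inputs from the article (Participants):** SD 33 and mean 52 in the standard-of-care group at one year; target difference 10; 125 per group. **Assumptions, not in the article:** share attending, prognostic gap between attenders and non-attenders, and correlation r between attendance and outcome. Higher scores are taken as worse.

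**1. Does complete-case respond to compliance?** A large simulated trial had 70% attendance, r = 0.3, a true effect of 10 in attenders and none in non-attenders, and every outcome observed. ITT gives 6.98, or 7.0, which agrees with 0.70 × 10. Complete-case uses the same patients and gives the same 7.0. It carries no information on compliance.

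**2. Per-protocol under no effect, simple form.** If attenders are compared with an intact control arm, the control mean contains would-be non-attenders and the programme mean does not. Hence

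bias = (share of non-attenders) × (their prognostic deficit)

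- 20% non-attenders, 10 points worse: 0.20 × 10 = 2.0 points
- 30% non-attenders, 10 points worse: 0.30 × 10 = 3.0 points

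That is 20-30% of the 10-unit target. If non-attenders were 10 points better, the same sums give 2-3 points against the programme.

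**3. The same bias from a correlation.** With attendance share p,

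bias = 33 × r × φ(z₁₋ₚ) / p

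and the rejection rate follows from SE = 33 × √(1/125 + 1/(125p)). Each cell shows spurious points, then the share of null trials in which a two-sided 5% test rejects.

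| r | p = 90% | p = 80% | p = 70% | p = 60% |
|---|---|---|---|---|
| 0.1 | 0.64; 5.3% | 1.15; 5.8% | 1.64; 6.5% | 2.12; 7.3% |
| 0.2 | 1.29; 6.0% | 2.31; 8.2% | 3.28; 11.0% | 4.25; 14.3% |
| 0.3 | 1.93; 7.4% | 3.46; 12.3% | 4.92; 18.8% | 6.37; 26.2% |

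The two forms agree. At r = 0.2 the implied gap is 3.28 / 0.30 = 10.9 points at 70% attendance and 2.31 / 0.20 = 11.6 at 80%, so a 10-point gap corresponds to r a little below 0.2.

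All these figures are unadjusted. Baseline adjustment removes whatever part of the gap already shows in the baseline score. At the zero correlation used for the sample size it would remove nothing, but the article calls that value conservative, so some reduction should be expected.

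**4. The alternative.** In the trial of step 1, attenders versus all controls gives 14.93, which is the true 10 plus 4.93 of selection. The instrumental-variable estimate, ITT difference / difference in attendance, gives 6.98 / 0.70 = 10.0. With no true effect the same set-up gives 4.93 for attenders versus controls and −0.02 for the instrumental-variable estimate.

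The price is precision. At 70% attendance and 125 per arm, approximately:

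- ITT SE = 33 × √(2/125) = 4.17
- complier-average SE = 4.17 / 0.70 = 5.96
- per-protocol SE = 33 × √(1/125 + 1/87.5) = 4.60

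The interval is then about 5.96 / 4.60 = 1.30 times as wide as the per-protocol one.

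**The case against.** **The per-protocol set is undefined.** A reader might infer that the plan compares attenders with all controls. The article does not say so, and defining the set is commonly left to the SAP. Dental-care seeking is recorded and dental register data will be obtained, so controls who found comparable care could be excluded too. This stands: an intact control arm is a working assumption of the calculations, not something the plan states. But excluding care-seeking controls is a second, different selection. It does not restore comparability, and covariate adjustment helps only for measured factors.

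**The direction is not settled.** A reader might infer that per-protocol must favour the programme. The documents do not support that. Visits are free and tailored to oral problems, so patients with worse symptoms might attend more, which would reverse the bias. This stands in full.

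**These are only sensitivity analyses.** This also stands. ITT governs the main analyses, and the wording leaves room for other analyses. A reader who inferred that the primary conclusion is at risk would be wrong.

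**Complete-case may be meant for failure to complete follow-up**, since non-adherence and non-retention are registered together. That is a fair reading, but non-retention is a missing-data question, so the label still needs correcting. Correcting it changes no result.

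**The complier-average estimate has its own assumption.** Allocation must act on the outcome only through the chosen exposure. A cut-off such as 3 of 4 visits violates this if one or two visits help, and would inflate the estimate. The Discussion also says that blinding is not feasible and that patients aware of the intervention may report more favourably, which is a path outside attendance. This stands. It is why visit count is preferable to a threshold and why the assumption must be written down.

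**Conclusion.** The point holds at modest severity. Complete-case is given a purpose that it cannot serve. Per-protocol is a weak tool here because the visit schedule exists in one arm only, and nothing else in the article repairs that.

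The size is unknown. The 2-3 points rest on an assumed 20-30% of non-attenders, an assumed 10-point deficit, no baseline adjustment and an intact control arm. The wider range of 0.6 to 6.4 points rests on assumed correlations of 0.1-0.3 and attendance of 60-90%. Only the dependence is firm: if attendance is related to prognosis, the estimate is biased, in whichever direction that relation runs. The ITT primary analysis and its conclusion are not touched.

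**What to change.** - **Add** for the non-compliance question a complier-average causal effect by two-stage least squares: randomised arm as instrument, number of programme visits attended by 12 months as exposure, the primary ANCOVA covariates, and robust standard errors as in the primary model. A threshold version should be secondary only.
- **State** the assumption that allocation affects the outcome only through attendance, and that unblinded, patient-reported outcomes put it under strain. A visit-count model also takes the effect as roughly proportional to visits when it is scaled up to full attendance.
- **Relabel** complete-case as a sensitivity analysis for the multiple-imputation, missing-at-random handling.
- **If per-protocol is kept**, define it for both arms before results are seen and report it as descriptive.

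The cost is wording in the analysis plan and one further model. Non-adherence is already registered, so the main check is that attendance is held as a visit count. The interval will be wider, by about 30% than the per-protocol one at an assumed 70% attendance. In return, the estimate cannot show an effect where the ITT difference is zero.

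### The economic evaluation stops at one year, about a third of a three-year programme, so its ICER cannot stand for the whole programme

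*Protocol article*

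**What the plan says.** All references are to the protocol article.

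- **Horizon** (Data processing and analysis): "The economic evaluation will estimate societal costs over a one-year time horizon for each patient; no discounting will therefore be necessary in these analyses". The section does not say when the year begins. The results are to be reported as an ICER per QALY, a cost-effectiveness plane and acceptability curves. The sensitivity analyses given as examples vary prices, the value set and patient heterogeneity, not the horizon.
- **Programme** (Intervention and standard of care): "The intervention starts 6 months after completion of RT and ends after the 3-year follow-up". The contact schedule is: "Every 3 months, participants in the intervention group are scheduled for an appointment with a dental hygienist".
- **Outcome data** (Data collection overview): questionnaires, including the EQ-5D-3L and the EORTC core questionnaire from which QALYs are to be derived, are collected at baseline and "6 months after the end of treatment (randomisation and start of intervention), and 1, 2 and 3 years after randomisation".
- **Register data** (same section): "The collected register data will cover the period from one year prior to diagnosis to five years after the completion of treatment".
- **Cost components** (Data processing and analysis): after specialised care, drugs and formal assistance, the list continues with "costs for dental care, and indirect costs in the form of productivity loss for sickness absence". On reporting: "Societal costs will be reported, as well as costs by components and payers".

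**The concern.** The stated aim is to prevent or lessen late oral complications, and the Background notes that caries becomes more common over time after radiotherapy. The Discussion presents long follow-up as what sets this trial apart from earlier ones, none of which went beyond a year. It also gives the economic evaluation weight because financial incentives drive decisions on adopting new methods. Whoever decides on adoption will be deciding about the programme as designed, which is about three years of visits. An evaluation cut off at one year leaves out the costs of the second and third years, and any avoided treatment, sickness absence or QALY gain that appears in them.

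At stake is how the ICER is interpreted. If the one-year figure is taken as the value for money of the programme, the decision rests on an unstated assumption that the balance of cost and benefit in later years is the same as in year 1.

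**Working it through.** The plan gives no unit cost, QALY gain or ICER, so there is no economic figure to reproduce. Two things can be checked: how much of the programme the horizon covers, and how far a one-year ICER can lie from a three-year one.

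**Step 1. Coverage.** Inputs from the protocol: duration about 36 months from randomisation, visit interval 3 months, horizon 12 months. Assumption: the year starts at randomisation.

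- Scheduled visits in the programme: 36 / 3 = 12 (13 if one falls on the start date).
- Visits within the horizon: 12 / 3 = 4 (5 if one falls on the start date).
- Share: 4/12 = 33% (5/13 = 38%).

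**Step 2. Are later data available?** The last visit is 6 + 36 = 42 months after the end of treatment. The register window runs to 60 months after treatment, so it covers the full three years. Health status is measured at 1, 2 and 3 years after randomisation. A three-year horizon needs no new data source.

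**Step 3. One-year against three-year ICER.** Let the incremental cost be c in each year (assumed equal), the QALY gain in year k be g_k, and the yearly discount factor be d = 1/(1+r), with year 1 undiscounted.

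- ICER over 1 year = c / g_1
- ICER over 3 years = c(1 + d + d²) / (g_1 + d·g_2 + d²·g_3)

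Worked example, gain rising 0.5 : 1 : 1.5 with r = 0: one year gives c/0.5 = 2c; three years gives 3c/3 = c; ratio 2.0. For a fading gain of 1 : 0.5 : 0.25, one year gives c; three years gives 3c/1.75 = 1.714c; ratio 0.58.

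The gain profiles and the discount rates are assumptions; the protocol gives neither.

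| Assumed QALY gain, years 1 : 2 : 3 | Ratio of 1-year to 3-year ICER at r = 0%, 3%, 5% |
|---|---|
| 1 : 1 : 1 (constant) | 1.00, 1.00, 1.00 |
| 0.5 : 1 : 1.5 (rising) | 2.00, 1.98, 1.97 |
| 1 : 0.5 : 0.25 (fading) | 0.58, 0.59, 0.60 |
| 1 : 0 : 0 (year 1 only) | 0.33, 0.34, 0.35 |
| 0 : 1 : 2 (none in year 1) | 1-year ICER undefined |

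The discount rate hardly matters over three years. The time profile of the benefit decides the answer, and a one-year analysis cannot show that profile.

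**The case against.** The strongest defence is that one year is a coherent choice. It matches the 12-month primary comparison, it makes the absence of discounting correct, and it gives an earlier result with less missing data. A one-year ICER is a valid summary of the first programme year, and the article never says that it will be presented as the value of all three years. This stands, and it is why the one-year analysis should be kept. It does not remove the gap: the clinical analysis has its primary comparison at 12 months but is repeated at every follow-up, while the economic evaluation has no longer counterpart. It is also fair to say that an article condenses a fuller plan. The horizon, however, is not left open here. It is stated outright, and the lack of discounting is derived from it.

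Two stronger readings are tempting, and the document supports neither.

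- **That the programme's own visits are left uncosted.** A reader might infer this because the cost list does not name them and the article says "All visits to the dental hygienist are at no cost". In context that sentence is about what the participant pays; the next one turns to treatment by a dentist, which the participant does pay for. The list includes dental care without restriction, the perspective is societal, and costs are to be split by payer. The visits are neither named nor excluded, and the document does not show whether they will appear in the dental registers. This is a point to clarify, not an omission.
- **That truncation biases the result against the programme.** A reader might infer this because prevention costs come first and benefits later. The rise in caries over time does not say how the difference between arms in QALYs or costs develops. The table in the working shows that the one-year ICER can be too high, too low or the same.

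**Conclusion.** The point holds as a limit on what the planned evaluation can answer. A one-year horizon covers about one third of the programme (33%, or 38% if a visit falls on the start date), with no stated reason and no longer analysis listed, although the data for one are already planned. The resulting ICER describes the first programme year only. Across the profiles tried where it is defined, it lies between about 0.33 and 2.0 times the three-year ICER; it is undefined if nothing is gained in year 1.

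These figures rest on equal yearly incremental cost, on illustrative gain profiles, on the year starting at randomisation, and on QALYs being taken over the same year as costs, which the text implies but does not spell out. The 4-of-12 coverage needs only the start-date assumption and the visit schedule.

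It would go too far to call the one-year ICER wrong or the lack of discounting an error, or to put a monetary size on the problem, since the document has no unit cost or QALY gain to support one. Costs are one of several secondary outcomes, and the primary analysis is not affected.

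**What to change.** In Data processing and analysis:

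1. Add a pre-specified three-year within-trial cost-effectiveness analysis from randomisation, with costs and QALYs in years 2 and 3 discounted and the rate stated.
2. Keep the one-year analysis beside it as the counterpart of the 12-month primary comparison, and state when its year begins. Which of the two is called the base case is open to debate; both should be fixed before the data are seen.
3. State that the one-year ICER refers to the first programme year and will not be presented as that of the whole programme.
4. As a clarification, state that the programme's hygienist visits are counted under dental care costs.

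The cost is protocol wording and additional analysis, with no new data collection for the longer horizon. The three-year result will come later and carry more missing data than the one-year result; the plan already provides for imputation in the economic evaluation where needed.
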